## Abstract

**Background:**

Diabetes and obesity have reached epidemic proportions in the U.S. with rates consistently higher among Hispanics as compared to non-Hispanic whites. Among Hispanic women diagnosed with gestational diabetes mellitus (GDM), 50% will go on to develop type 2 diabetes within 5 years of the index pregnancy. Although randomised controlled trials among adults with impaired glucose tolerance have shown that diet and physical activity reduce the risk of type 2 diabetes, such programs have not been tested in high-risk postpartum women. The overall goal of this randomised controlled trial is to test the efficacy of a culturally and linguistically modified, individually-tailored lifestyle intervention to reduce risk factors for type 2 diabetes and cardiovascular disease among postpartum Hispanic women with a history of abnormal glucose tolerance during pregnancy.

**Methods/Design:**

Hispanic pregnant women who screen positive for GDM will be recruited and randomly assigned to a Lifestyle Intervention (n = 150) or a Health & Wellness (control) Intervention (n = 150). Multimodal contacts (i.e., in-person, telephone, and mailed materials) will be used to deliver the intervention from late pregnancy (29 weeks gestation) to 12 months postpartum. Targets of the intervention are to achieve Institute of Medicine Guidelines for postpartum weight loss; American Congress of Obstetrician and Gynecologist guidelines for physical activity; and American Diabetes Association guidelines for diet. The intervention draws from Social Cognitive Theory and the Transtheoretical Model and addresses the specific cultural and environmental challenges faced by low-income Hispanic women. Assessments will be conducted at enrollment, and at 6-weeks, 6-months, and 12-months postpartum by trained bicultural and bilingual personnel blinded to the intervention arm. Efficacy will be assessed via postpartum weight loss and biomarkers of insulin resistance and cardiovascular risk. Changes in physical activity and diet will be measured via 7-day actigraph data and three unannounced 24-hour dietary recalls at each assessment time period.

**Discussion:**

Hispanic women are the fastest growing minority group in the U.S. and have the highest rates of sedentary behavior and postpartum diabetes after a diagnosis of GDM. This randomised trial uses a high-reach, low-cost strategy that can readily be translated into clinical practice in underserved and minority populations.

**Trial registration:**

NCT01679210

## Background

Type 2 diabetes is a global epidemic affecting approximately 21 million people in the U.S. [1]. The age at onset for type 2 diabetes has decreased [1], highlighting the importance of identifying high-risk groups early, in order to implement prevention efforts. One such high-risk group is women who develop glucose intolerance during pregnancy. Both gestational diabetes mellitus (GDM) and milder glucose intolerance in pregnancy identify women who are at high risk for type 2 diabetes [2,3]. Indeed, a recent meta-analysis found that GDM confers a 7-fold risk for future type 2 diabetes [4] and up to one third of women with type 2 diabetes have previously been diagnosed with GDM [5].

According to a recent systematic review, the highest risk period for the development of type 2 diabetes is within the first 5 years after a GDM pregnancy [2], with 50% of Hispanic women developing type 2 diabetes within 5 years [6]. This is consistent with recent findings showing a rapid postpartum change in glucose tolerance [7]; by 12 months postpartum, 17.1% of those with recent GDM and 10% of women with milder degrees of gestational glucose intolerance had progressed to prediabetes or diabetes [8]. In other words, pregnancy unveils a preexisting susceptibility for type 2 diabetes and offers the opportunity to implement interventions to decrease such risk.

In spite of these observations, studies of diabetes prevention among high-risk postpartum women with history of GDM are sparse. In the Diabetes Prevention Program (DPP) [9] women with a history of GDM, approximately a decade after their pregnancy, were able to decrease their diabetes risk with a weight reduction goal of 7% of their baseline weight even though they lost less weight than the overall DPP sample (1.60?±?0.80 kg vs. 4.03?±?0.40 kg at 3 years, p?=?0.021) [10]. This weight loss was achieved through behavioral goals of ≥150 min per week of physical activity and a low-fat, low-calorie diet. However, this trial involved an intensive intervention not easily administered in a clinical setting and was conducted an average of 12 years after GDM diagnosis such that women with early postpartum conversion to diabetes, and therefore at highest risk, were not eligible. Other limitations included intervening lifestyle factors and subsequent pregnancies which may have modified findings, reliance on self-reported diagnosis of GDM, lack of laboratory measures on glucose tolerance during pregnancy, as well as a small percentage of Hispanic women.

Weight loss can be achieved in the immediate postpartum period [11], with studies finding that both energy intake restriction and physical activity are needed to reduce weight [12,13], compared to exercise alone [14]. Similarly, weight loss interventions among non-pregnant adults [15-17] have shown that multifaceted interventions compared with stand-alone dietary advice, exercise modification, or behavioral strategies yield significant improvements in health outcomes and weight loss. A recent review calculated that lifestyle interventions for women with a history of GDM have the potential to delay or prevent one-sixth of type 2 diabetes cases in the female population [18].

Hispanics are the largest minority group in the U.S., with the highest birth and immigration rates of any minority group [19]. It is estimated that by 2050, Hispanic women will comprise 30.2% of the female population in the United States [20]. Hispanics are the most physically inactive ethnic group in the U.S. [21] and are disproportionately affected by overweight and obesity. At each BMI level, Hispanics have a higher prevalence of diabetes than non-Hispanic whites [22-24]. Furthermore, a significant proportion of Hispanics lack awareness of diabetes risk factors and prevention strategies [25]. Despite the high rates of progression of GDM to type 2 diabetes, only one in five Hispanic women receive recommended postpartum diabetes screening, the lowest follow-up frequency for any group [26]. Due to cultural factors, socioeconomic circumstances, differences in educational background, and language barriers, Hispanics have had limited access to clinical and public health interventions that promote healthy lifestyles. Therefore, the overall objective of this trial is to test the ability of a lifestyle intervention, informed by formative behavioral research, to reduce risk factors for type 2 diabetes and cardiovascular disease among postpartum Hispanic women with a recent history of abnormal glucose tolerance (AGT) during pregnancy.

### Aims

Specific aims are to achieve the Institute of Medicine (IOM) guidelines for postpartum weight loss and to improve maternal metabolic status by achieving and maintaining 1) postpartum weight reduction to prepregnancy weight if prepregnancy BMI was in the normal range, or to achieve a 5% reduction from prepregnancy weight if prepregnancy BMI was overweight/obese [27]; 2) at least 150 min per week of moderate intensity physical activity such as brisk walking, as recommended by ACOG for the postpartum period [28]; and 3) reduction in postpartum total energy intake via reduced consumption of popular energy-dense foods (e.g., fast food, high-fat snacks, fried foods and sugar-sweetened beverages), reduced portion size, appropriate modifications in ethnic recipes, and higher fruit and vegetable intake, as recommended by the ADA [29].

## Methods

Estudio Parto (Project Aiming to Reduce Type twO diabetes) will be based at the ambulatory obstetrical practices of Baystate Medical Center in Western Massachusetts. Eligible pregnant Hispanic women who screen positive for GDM will be recruited between 24-28 weeks gestation and randomly assigned to a Lifestyle Intervention (n = 150) or a Health & Wellness (control) Intervention (n = 150). Multimodal contacts (i.e., in-person, telephone counseling, and mailed print-based materials) will be used to deliver the intervention from late pregnancy (29 weeks gestation) to 12 months postpartum, encompassing introductory, active, and maintenance phases (Figure 1).

**Figure 1 F1:**
[figure not shown]
Trial design.

### Eligibility criteria

Baystate Medical Center practices universal screening for GDM, which consists of a random 50-g glucose load and a plasma glucose determination 1 hour later. If the plasma glucose value is ≥135 mg/dL, a diagnostic 100-g 3 hour oral glucose tolerance test (OGTT) is conducted. Eligible participants will be pregnant Hispanic women who screen positive for GDM (50-g glucose load ≥135 mg/dL). We will exclude women with: 1) history of type 1 or type 2 diabetes, heart disease, or chronic renal disease, 2) contraindications to postpartum participation in the trial’s intervention activities which include engagement in moderate physical activity and consumption of a low-fat/high-fiber diet (e.g., Crohn’s disease, ulcerative colitis), 3) inability to read English or Spanish at a 6th grade level, or 4) <18 or >45 years of age.

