### Randomisation

Randomisation to the Lifestyle Intervention or to the Health & Wellness (control) Intervention will occur at ~29 weeks gestation, after completion of the baseline assessment. Randomisation will be stratified based on the results of the diagnostic 100-g OGTT using thresholds defined by the American Diabetes Association (ADA) [31] (≥ 95 mg/dL fasting and?≥?180 mg/dL, ≥155 mg/dL and ≥140 mg/dL at 1 hour, 2 hours and 3 hours, respectively): 1) no glucose values meeting or exceeding the ADA thresholds; or 2) one or more glucose values meeting or exceeding the ADA thresholds.

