**Eligibility variables**				
100 g OGTT (prenatal)	X			

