### Data analysis

Primary analyses will evaluate differences in the change from 6 weeks postpartum to 12 months postpartum between the groups (an intent to treat analysis) in postpartum weight loss (aim #1), biomarkers of insulin resistance (aim #2), and biomarkers of cardiovascular disease risk (aim #3). We will use mixed models with random subject effects, including a common mean at baseline for the treatment groups, a period effect, and an intervention by period interaction [60]. The mixed model analysis will enable inclusion of time varying covariates such as breastfeeding behaviors, depression, and sleep, which may vary between baseline and follow-up for individuals. Equivalence of treatment groups will be assessed by comparing distributions of the potential confounders across groups. In addition, we will investigate established risk factors for type 2 diabetes as potential confounders or effect modifiers. Important potential effect modifiers include prepregnancy BMI, and breastfeeding behaviors. Mixed model analyses will also be used to account for the repeated measures of exercise and diet and will be used to evaluate adoption and maintenance of behavior change (aim #4) in the Lifestyle Intervention group.

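### Abnormal glucose tolerance, the population in the objective, is never defined, and the stated analysis leaves out the OGTT group that randomisation is stratified on

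*Protocol article*

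**What the plan says.** **Entry.** Under Eligibility criteria, the rule is "Eligible participants will be pregnant Hispanic women who screen positive for GDM (50-g glucose load ≥135 mg/dL". The Abstract and the opening of Methods describe the same population, women with a positive GDM screen. The Eligibility section says that a positive screen leads to a diagnostic 100-g OGTT, but sets no OGTT result as a condition of entry.

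**Randomisation.** The strata are "1) no glucose values meeting or exceeding the ADA thresholds; or 2) one or more glucose values meeting or exceeding the ADA thresholds".

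**Table 1.** The row "100 g OGTT (prenatal" stands under the eligibility heading.

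**Objective.** The Background states it for "postpartum Hispanic women with a recent history of abnormal glucose tolerance (AGT) during pregnancy". The Abstract and the Discussion also speak of abnormal glucose tolerance. None of them attaches a glucose criterion to the term.

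**Rationale.** The Background cites progression by 12 months: "17.1% of those with recent GDM and 10% of women with milder degrees of gestational glucose intolerance had progressed to prediabetes or diabetes". It does not say whether a positive screen with a normal OGTT belongs to the milder group.

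**Analysis.** Data analysis lists a mixed model with random subject effects, a common baseline mean, a period effect and a treatment-by-period term. It then says "Important potential effect modifiers include prepregnancy BMI, and breastfeeding behaviors". OGTT group appears in neither place, although Covariates says that the degree of prenatal glucose abnormality is recorded.

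**The concern.** A reader of the results will want to know to whom they apply. A woman with a 50-g value just over the cut-off and four normal OGTT values is eligible and has a stratum, yet no value on her diagnostic test is abnormal. The article does not say whether she belongs to the AGT population or is enrolled alongside it.

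The investigators evidently thought OGTT status mattered, since it is the one factor they stratify on. The stated analysis then gives a single effect averaged over both strata. If that average is reported as the effect in women with AGT, nothing the article commits to shows whether it holds in women with an abnormal diagnostic test. This matters most for the second aim, whose glucose and insulin markers could plausibly respond differently by glucose status.

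**Working it through.** **1. The passages side by side.**

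| Place | What defines the population |
|---|---|
| Abstract (Methods/Design), Methods opening, Eligibility criteria | Positive 50-g screen |
| Randomisation | Both OGTT-normal and OGTT-abnormal women |
| Table 1 | 100-g OGTT listed as an eligibility variable |
| Abstract (Background), Background, Discussion | AGT, with no criterion |

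The first two rows agree: screen-positive women enter whatever their OGTT shows. The third row labels as an eligibility variable a test for which no entry threshold exists. The fourth uses a term that could mean either the screen or the diagnostic test.

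**2. The plan's own sample size.** Inputs from Power and sample size: 0.35 to 0.40 SD, 80% power, 0.05 level (taken as two-sided), 128 per arm, 15% attrition.
- n per arm = 2 × (1.960 + 0.842)² / 0.35² = 128.2, rounded up to 129, against 128 stated.
- At 0.40 SD the requirement is 99 per arm. Power with 128 per arm is 80.0% at 0.35 SD and 89% at 0.40 SD.
- Recruitment: 256 / 0.85 = 301.2, rounded up to 302, against 300 stated.

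The figures reproduce. At 0.35 SD all 256 women are needed, so there is no reserve.

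**3. Precision in the OGTT-abnormal stratum.** The documents do not give the share *a* of women with at least one abnormal value, so a range is assumed. With n = 128*a* per arm, SE = √(2/n) in SD units and power = Φ(effect/SE − 1.960).

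| Assumed *a* | n per arm | SE | Power at 0.35 / 0.40 SD |
|---|---|---|---|
| 80% | 102 | 0.140 | 71% / 82% |
| 60% | 77 | 0.161 | 58% / 70% |
| 50% | 64 | 0.177 | 51% / 62% |
| 40% | 51 | 0.198 | 43% / 53% |
| 20% | 26 | 0.280 | 24% / 30% |

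At *a* = 50% the 95% interval is the estimate ± 1.960 × 0.177 = ± 0.35 SD. The difference between strata has SE √(0.177² + 0.177²) = 0.25 SD, so 80% power needs a difference of 2.802 × 0.25 = 0.70 SD.

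**4. Overall power under different patterns of effect.** The overall SE is √(2/128) = 0.125. Take *a* = 50% and a true effect of 0.35 / 0.40 SD in OGTT-abnormal women.
- Equal effect in OGTT-normal women: 80% / 89%, whatever the mix.
- Half the effect: the average is 0.35 × 0.75 = 0.2625 or 0.40 × 0.75 = 0.30, and power is 56% / 67%.
- No effect: the average is 0.175 or 0.20, and power is 29% / 36%.

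Nothing in the documents chooses among these patterns.

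**The case against.** The strongest reply is that the broad population is deliberate and consistently applied. Abstract, Methods and Eligibility all use the positive screen, Randomisation names OGTT-normal women as a stratum, and the Background extends the rationale below GDM. On that view AGT simply means screen-positive. This reading is available and may well be the intended one, but the article never states it.

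On the analysis, Data analysis also says that known risk factors for type 2 diabetes will be examined as confounders or modifiers, and its list of modifiers is not closed. OGTT status could fall under that sentence, and an article may leave modelling detail to a fuller document. This stands in part: the factor is not excluded. But the article does set out its model terms and does name its important modifiers, and the only factor it stratifies on is in neither list. What the target population is, and how Table 1 relates to the entry rule, are protocol content.

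Three stronger readings are tempting.
- *The overall result cannot answer the AGT objective.* This requires AGT to mean an abnormal OGTT value, which the documents do not say. Stratified randomisation also protects a comparison within that stratum.
- *The effect will be diluted.* This needs both a stratum share and a smaller effect in OGTT-normal women, and the documents give neither. Weight loss, the first aim, has targets set by prepregnancy BMI and not by OGTT status.
- *Women who miss the OGTT are eligible but have no stratum.* Eligibility criteria says the test follows a positive screen, and Randomisation uses its result, so a result before allocation is already implied. The case is mostly hypothetical.

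**Conclusion.** The point holds as one of definition and of an unused stratification factor. AGT is undefined. The entry rule, the strata, the Table 1 heading and the objective must be reconciled on whether screen-positive women with a normal OGTT belong to the target population. The stated model and named modifiers omit the OGTT group, so no committed analysis shows whether the overall effect holds in women with an abnormal diagnostic test.

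There is no error in the sample size, and the primary intent-to-treat comparison of all randomised women remains valid. The scenario powers in the working show what heterogeneity could do; they do not predict it.

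A reader might also infer that every conclusion about AGT should rest on the OGTT-abnormal stratum. That would move the main claim from a comparison with about 80% power at 0.35 SD to one with about 24% to 71% over the assumed shares, and the documents give no reason to accept that trade.

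**What to change.** 1. In Data analysis, include the OGTT randomisation stratum in the mixed model and pre-specify it as an effect modifier. Report the treatment effect with a confidence interval in each stratum, as a supporting result beside the primary intent-to-treat effect in all randomised women.
2. Either describe the overall population as women with a positive 50-g GDM screen, or state that AGT as used here includes them. Which glucose criterion should govern entry is for the investigators; the wording need only agree across the sections.
3. Align the Table 1 heading over the 100-g OGTT with Eligibility criteria, for example by labelling it a stratification variable if that is its role.

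The cost is wording, one added model term, one interaction and two stratum estimates from data already collected. No extra recruitment or testing is needed. The downside is imprecision: with half the women OGTT-abnormal (assumed), the stratum interval is about ± 0.35 SD and only a very large difference between strata would be detected. The report should say that a non-significant interaction does not show equal effects, and that the stratum results support the overall conclusion and do not replace it.

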### Recruitment

The trial will capitalize on our expertise in culturally appropriate strategies for recruiting pregnant Hispanic women in practice-based settings [30]. Specifically, bilingual (Spanish and English) and bicultural health educators will recruit women at the time of routine GDM screening. Women will be informed of the aims and procedures of the project and will be asked to sign a written informed consent form, as approved by the Institutional Review Boards of the University of Massachusetts-Amherst and Baystate Health. Upon enrollment, the baseline assessment will be conducted which includes: 1) data collection of behaviors during pregnancy via standardized questionnaires, 2) measures of physical activity via an ActiGraph GT3X-plus activity monitor (Actigraph LLC, Pensacola, FL) to be worn on the wrist for the next 7 days, 3) measures of dietary intake via three unannounced 24-hr dietary recalls over the following two-week period, 4) laboratory measures of biomarkers of insulin resistance and cardiovascular risk via a study-specific fasting blood sample. Completion of each assessment and blood draw is followed by a gift card.

### Randomisation

Randomisation to the Lifestyle Intervention or to the Health & Wellness (control) Intervention will occur at ~29 weeks gestation, after completion of the baseline assessment. Randomisation will be stratified based on the results of the diagnostic 100-g OGTT using thresholds defined by the American Diabetes Association (ADA) [31] (≥ 95 mg/dL fasting and?≥?180 mg/dL, ≥155 mg/dL and ≥140 mg/dL at 1 hour, 2 hours and 3 hours, respectively): 1) no glucose values meeting or exceeding the ADA thresholds; or 2) one or more glucose values meeting or exceeding the ADA thresholds.

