### Covariates

Clinical characteristics of the current pregnancy and medical history will be abstracted from the pregnancy medical record (Table 1). Weight is measured prospectively at each prenatal visit and postpartum weight will be measured during assessment visits by trained study staff to the nearest 0.1 kg on accurately calibrated standard clinical scales using a standardized protocol. Gestational age will be based upon the best clinical estimate as recorded in the medical record. Adherence with gestational weight gain guidelines will be calculated by comparing the observed weight gain with the 2009 IOM Guidelines [27]. We will also collect gestational age at the time of GDM screen; degree of abnormality on glucose tolerance testing during pregnancy; treatment for glucose abnormality during pregnancy (e.g., diet, oral hypoglycemic agents and/or insulin); pregnancy complications; and birth outcomes.

Sociodemographic factors will be collected via self-report at enrollment. Acculturation will be assessed via the Psychological Acculturation Scale [55], language preference, and generation in the U.S. Smoking will also be assessed via the biomarker cotinine. Postpartum factors will be collected via self-report at each postpartum assessment and will include: The Pittsburgh Sleep Quality Index (PSQI) [56], the Edinburgh Postpartum Depression Scale [57,58], and the Infant Feeding Questionnaire [59].

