### Power and sample size

The study is powered to detect mean differences in change in outcome variables from baseline in the Lifestyle Intervention as compared to the Health and Wellness (control) Intervention that are equivalent to 0.35 to 0.40 standard deviations, or a “small-medium” effect size [61], at 80% power at a 0.05 level of significance. A total of 256 women are required (128 participants per study arm). With an expected attrition rate of 15%, 300 eligible women will be recruited.

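### Randomisation is stratified by the 100-g OGTT result, but the stated primary mixed model has no term for the stratum; adding it is a free, small gain in precision if the stratum predicts change

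*Protocol article*

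**What the plan says.** Under Randomisation, the article states: "Randomisation will be stratified based on the results of the diagnostic 100-g OGTT". The two strata are "1) no glucose values meeting or exceeding the ADA thresholds; or 2) one or more glucose values meeting or exceeding the ADA thresholds". The stratum must therefore be known for each woman when she is randomised.

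Under Data analysis, the target is set as follows: "Primary analyses will evaluate differences in the change from 6 weeks postpartum to 12 months postpartum between the groups". The model is a mixed model with random subject effects, "including a common mean at baseline for the treatment groups, a period effect, and an intervention by period interaction". The section then names breastfeeding, depression and sleep as time-varying covariates, and prepregnancy BMI and breastfeeding as important effect modifiers. The OGTT stratum is in none of these lists.

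Two other sentences come close. Data analysis adds that "we will investigate established risk factors for type 2 diabetes as potential confounders or effect modifiers", and Covariates lists "degree of abnormality on glucose tolerance testing during pregnancy" among the data to be collected. Neither puts the stratum into the primary model.

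**The concern.** Stratified allocation keeps the arms balanced on the stratum, so differences between strata no longer add to the sampling variance of the treatment effect. A model without the stratum still counts those differences as residual variance. If the stratum predicts the analysed change, the reported standard error then exceeds the true one. Confidence intervals are wider than necessary and the test rejects less often than its nominal level.

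The sentence on confounders is unlikely to fix this. A search for confounders looks for imbalance between arms, and this factor is balanced by design. The reason to include it is a correct standard error, not confounding.

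An effect of the stratum on change is more plausible for the glucose and insulin outcomes of aim 2 than for weight in aim 1. At stake is a modest amount of precision.

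**Working it through.** **Inputs.** From Power and sample size: 128 per arm, a difference "equivalent to 0.35 to 0.40 standard deviations", "at 80% power at a 0.05 level of significance", 15% attrition and 300 recruited. Sidedness is not stated; two-sided reproduces the plan's figure (one-sided would need 101 per arm). The share R² of the variance of the analysed change that the stratum explains is not given, so it is varied from 0 to 0.20 as an assumption.

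**The plan's own figure.** n per arm = 2(1.960 + 0.842)²/0.35² = 128.1, rounded up to 129 (258 in total) against 128 (256) stated. At 128 per arm, 0.35/√(2/128) = 0.35/0.125 = 2.80 and power = Φ(2.80 − 1.96) = 80.0%. For attrition, 256/0.85 = 301.2, so 302 against 300 stated. The stated size reproduces within rounding and does not depend on the stratum.

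**Adding the stratum.** Let f = √(1 − R²), with the unadjusted SD set to 1.

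- Overstatement of the unadjusted SE: 1/f − 1.
- Adjusted power: Φ(2.80/f − 1.96).
- Unadjusted power under stratified allocation: Φ((2.80 − 1.96)/f). The estimate already has the smaller true SE; only the reported SE is too large.
- Unadjusted type I error: 2(1 − Φ(1.96/f)).

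| Assumed R² | SE too large by | Type I error, unadjusted | Power, unadjusted | Power, adjusted |
|---|---|---|---|---|
| 0 | 0% | 5.0% | 80.0% | 80.0% |
| 0.01 | 0.5% | 4.9% | 80.1% | 80.4% |
| 0.02 | 1.0% | 4.8% | 80.2% | 80.7% |
| 0.05 | 2.6% | 4.4% | 80.6% | 81.9% |
| 0.10 | 5.4% | 3.9% | 81.2% | 83.9% |
| 0.20 | 11.8% | 2.8% | 82.6% | 87.9% |

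The power gain is 81.93 − 80.56 = 1.4 points at R² = 0.05 and 83.93 − 81.20 = 2.7 points at R² = 0.10.

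**If the stratum shifts every visit equally.** The baseline value then carries most of the stratum information. Let ρ be the correlation between visits and R² the stratum's share of variance at each visit. The correlation within strata is ρ′ = (ρ − R²)/(1 − R²), and the ratio of adjusted to unadjusted variance is (1 − R²)(1 − ρ′²)/(1 − ρ²). For ρ = 0.5 and R² = 0.10: ρ′ = 0.444, ratio 0.7222/0.75 = 0.963, SE 1.9% too large. For ρ = 0.9 and R² = 0.02 it is 0.05% too large. Over ρ from 0.5 to 0.9 and R² from 0.02 to 0.10, every value lies between these two.

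**Simulation of the common-baseline model.** There were 256 women, three visits with the first as baseline, correlation 0.7, half the women in each stratum, arms exactly balanced within strata, and 2,000 replicates. The adjusted model has a separate stratum effect at each visit.

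| Stratum effect | Model SE without stratum | Model SE with stratum | Ratio |
|---|---|---|---|
| None | 0.0893 | 0.0893 | 1.000 |
| Constant 0.4 SD | 0.0895 | 0.0892 | 1.003 |
| Growing from 0 to 0.4 SD | 0.0928 | 0.0891 | 1.042 |

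The last row agrees with the formula. The residual variance given baseline is 1 − 0.7² = 0.51 and the stratum adds 0.25 × 0.4² = 0.04, so R² = 0.04/0.55 = 7.3% and the SE ratio is √(0.55/0.51) = 1.038. Simulated power in that row was 83.8% without and 86.1% with the stratum. Each power figure has a Monte Carlo error of about √(0.86 × 0.14/2000) = 0.8 points, so the SE ratios are the firmer result.

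**The case against.** The best objection is that this argues from silence. A journal article condenses the full protocol, its list of model terms opens with a word that leaves room for others, and an unseen analysis plan may already contain the stratum. That stands as a limit: a reader might infer that the stratum has been ruled out, and the article does not say so. The point survives because the article goes beyond silence. It states a primary model and names covariates and effect modifiers, and the factor used for randomisation is in none of these lists.

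Three stronger readings are tempting and not supported.

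- **That the standard errors are certainly too large.** The article gives no reason for choosing this stratification factor and no measure of how well it predicts change. Its Background cites progression by 12 months of 17.1% after GDM and 10% after milder intolerance. That is suggestive, but the grouping is not that of the strata and no R² follows from it. With no effect on change there is no loss, and with a constant shift almost none.
- **That adjustment lifts power from 80.0% to 81.9-83.9%.** The unadjusted estimate already benefits from stratified allocation, so the fair starting point is 80.6-81.2%.
- **That a by-stratum treatment effect is a required result now missing.** One stratum has no abnormal 100-g value, so the question is reasonable. The trial is sized for the overall contrast, however, and the sentence on effect modifiers leaves room for exploring it.

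**Conclusion.** The point holds as a minor one. The model as stated does not carry the factor by which the women are randomised, and nothing else in the article commits to it. The consequence is conditional on the stratum explaining change beyond the baseline value. At an assumed R² of 5-10% the cost is an SE 2.6-5.4% too large and about 1.4 to 2.7 points of power. The error is conservative, so a positive result would not be undermined. The size of the gain rests wholly on the assumed R², since the article gives no value for it. The case for the change is that it analyses the trial by the groups it randomises by, at almost no cost.

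**What to change.** In Data analysis, prespecify the two-level OGTT randomisation stratum and its interaction with period as fixed effects in the primary mixed model for every outcome. The by-period term is needed because a main effect alone would miss an effect of the stratum on change. If the analysis plan already does this, a sentence in the protocol text is enough.

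The cost is one fixed effect per analysed visit, with no new data collection and no missing values, since the stratum is needed to randomise. In the simulation with no stratum effect the SE was 0.0893 with or without these terms, so nothing is lost if the stratum proves uninformative. A treatment-by-stratum estimate may be added, labelled exploratory.
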